### Sample size calculation

We rely on two approaches: First, for pilot studies and clinical trials, Julious [24] recommended to recruit at least 12 participants/group. Second, we performed a power analysis with G*Power [25] with the following statistical preconditions: Cohen’s f for ANOVAs with repeated measures and within and between interactions: 0.25; alpha: 0.05; Power: 0.8; number of groups: 3, number of measurements: 3; calculated total sample size: 36. To counterbalance possible drop-outs, the sample size was set at 45 participants; 15 participants per group.

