### Statistical analyses

Irrespective of which study conditions the patients are grouped to, at baseline, we will use Pearson’s correlations and univariate ANOVAs to examine the associations between the participants’ social and demographic background and their psychological wellbeing, sleep, QoL, and physical fitness. To examine whether and to what degree the three study conditions (endurance training, resistance training, active control) would impact the outcome variables over time, a series of ANOVAs for repeated measures with the following factors and dependent variables will be performed, namely, time (baseline; week-3 and week 6 since start of study); group (endurance training; resistance training; active control), and the time-by-group interaction; dependent variables: depressive symptoms, anxiety, stress, sleep complaints, QoL, cardiorespiratory fitness, and grip strength. Given the explorative character of the present study, we follow the previously reported recommendations [50, 51] and no correction of p-values for multiple testing would be performed. Data would be analyzed both per protocol and by intent-to-treat (ITT), with the last observation carried forward (LOCF). Patients will not be further followed up as regards the study questions, though, they would undergo routine checks every 6 months to monitor the development and recovery process of the HGG. The level of significance is set at alpha ≤ 0.05. All computations would be performed with the Statistical Package for the Social Sciences (SPSS)^®^ software (IBM Corporation, Armonk NY, USA) for Macintosh^®^.

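### LOCF is the only missing-data method named for the intent-to-treat ANOVA; it can bias the arm contrast by an unknown amount, and a mixed model on observed data would reduce or remove that bias

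*Protocol article*

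**What the plan says.** The Statistical analyses section plans "a series of ANOVAs for repeated measures with the following factors and dependent variables will be performed", with time (baseline, week 3, week 6), group (three arms) and their interaction. On analysis sets and missing values it has one sentence: "Data would be analyzed both per protocol and by intent-to-treat (ITT), with the last observation carried forward (LOCF"). I read LOCF as belonging to the intent-to-treat analysis. The section also says "All computations would be performed with the Statistical Package for the Social Sciences (SPSS") and "The level of significance is set at alpha ≤ 0.05".

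The Sample size calculation section plans on "ANOVAs with repeated measures and within and between interactions: 0.25; alpha: 0.05; Power: 0.8" and "number of groups: 3, number of measurements: 3; calculated total sample size: 36". It then adds: "To counterbalance possible drop-outs, the sample size was set at 45 participants; 15 participants per group". No drop-out rate is stated.

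Two other sections bear on who leaves. The Exclusion criteria list withdrawal, either by the patient or by a principal investigator who judges the patient unfit to continue on physical or mental grounds. Study harms links adverse events to a discussion of possible exclusion.

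**The concern.** LOCF is prescribed here, so this is not a detail left to a separate analysis plan. A patient who leaves before week 3 enters the week-6 comparison at the baseline score, with zero change. One who leaves between weeks 3 and 6 enters at the week-3 score. The repeated-measures ANOVA treats these constants as measurements.

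Drop-out may well be related to outcome. Physical and mental state can lead to withdrawal, and the outcomes measure the same things: depression, anxiety, quality of life, walking distance and grip strength. The per-protocol analysis is no safeguard, because it can also remove patients selectively.

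At stake is the time-by-group contrast. The Anticipated outcome section says positive results would support building exercise into clinical treatment of these patients.

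**Working it through.** **1. The plan's own figure.** Inputs from the Sample size calculation: f = 0.25, alpha 0.05, power 0.80, k = 3 groups, m = 3 measurements. Assumed, because the article states neither: correlation ρ = 0.5 and sphericity.

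λ = f²·N·m/(1−ρ) = 0.0625 × 36 × 3 / 0.5 = 13.5, with df1 = (k−1)(m−1) = 4 and df2 = (N−k)(m−1) = 66. Power is 0.823 at N = 36 and 0.781 at N = 33, so 36 with equal groups reproduces. The allowance is (45 − 36)/45 = 20%, and 36/(1 − 0.20) = 45.

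**2. What LOCF estimates.** Let d be the true six-week change in an arm (linear, SD units, higher is better), s1 the share lost before week 3 and s2 the share lost between weeks 3 and 6. If drop-out is unrelated to the patient's own course:

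E[LOCF change] = (1 − s1 − s2)·d + s2·d/2 = d·(1 − s1 − s2/2).

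**3. Numbers put in.** All drop-out rates and trajectories are assumptions.

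| Scenario | True contrast | LOCF contrast |
|---|---|---|
| All arms −1 SD; 30%/30%/10% (exercise/exercise/control) lost before week 3 | 0 | −0.70 − (−0.90) = +0.20 |
| Same losses, all arms −0.5 SD | 0 | −0.35 − (−0.45) = +0.10 |
| All arms −1 SD; same shares lost after week 3 | 0 | −0.85 − (−0.95) = +0.10 |
| Exercise +1.30, control flat; 20% lost before week 3 in each arm | 1.30 | 0.80 × 1.30 = 1.04 |
| Exercise flat, control −0.5; 10% + 10% lost in each arm | 0.50 | 0.85 × 0.50 = 0.425 |
| Exercise +0.5, control flat; 10% + 10% lost in each arm | 0.50 | 0.425 |
| Exercise flat, control −0.5; 20% + 20% lost in exercise only | 0.50 | 0.50 (no bias) |

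The 1.30 SD is the planning effect if both exercise arms gain linearly and control is flat. The interaction variance is then d² × (2/9) × (1/6) = d²/27, so d = 0.25 × √27 = 1.30.

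**4. Simulation of the planned ANOVA on LOCF data** (15 per arm, ρ = 0.5, 4,000 trials per scenario). The first row gave a false benefit of 0.20 SD and rejection in 8.3% of trials; a repeat gave 0.19 SD and 8.0%. The fourth row gave 1.04 SD and 79% power; the repeat gave 78%.

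**5. LOCF against a likelihood-based repeated-measures model** (unstructured covariance, 600 runs, standard error about 0.016). Drop-out was either completely at random (MCAR) or dependent on observed scores (MAR).

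| Scenario | True | LOCF, MCAR / MAR | Mixed model, MCAR / MAR |
|---|---|---|---|
| Control −0.5, exercise flat; 20% drop-out per arm | 0.50 | 0.44 / 0.42 | 0.51 / 0.49 |
| All arms −0.5; about 7% control, 28% exercise drop-out | 0 | 0.08 / 0.02 | −0.01 / 0.00 |
| All arms −1.0; same drop-out | 0 | 0.16 / 0.13 | −0.01 / 0.02 |

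**6. Drop-out driven by the patient's own worsening** (30%/30%/10%, no true effect, 300 runs, standard error about 0.02).
- Worst patients leave after week 3: their poor week-3 score is carried forward, and LOCF bias is −0.02 SD with a 0.5 SD decline and +0.02 SD with a 1 SD decline. A separate check gave −0.03 to +0.03.
- Worsening patients leave before week 3: LOCF shows a false benefit of 0.08 SD with no average decline and 0.17 SD with a 0.5 SD decline. The mixed model still shows 0.07 to 0.09 SD, because only the baseline was observed.

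**7. Fitness outcomes.** The Physical fitness section schedules the walking and grip tests at baseline and end only, whereas Table 1 adds week 3. On the former reading, every drop-out's carried fitness value is the baseline value.

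**The case against.** The strongest reply is that the document does not establish the harm. It gives no six-week trajectory, no drop-out by arm and no reasons for leaving. The Background describes the burden of the disease and a reduced level of quality of life, which is not a slope over six weeks, and the Statistical analyses section itself mentions recovery. A reader might infer that patients deteriorate during the trial, that leavers are mostly the worsening ones, and that LOCF therefore favours exercise. The text does not support that chain. If worsening patients leave after week 3 the bias is close to nil, and if scores are flat, unequal random drop-out causes none. The 0.20 SD figure needs early drop-out unrelated to worsening, a 1 SD decline, and three times the control drop-out in both exercise arms. This part of the reply stands.

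A reader might also set 79% power against the 91% that 45 complete patients would give. That overstates the loss: the plan promised 80%, and 36 complete patients give about 82%. Nor is the damage permanent, because the observed values remain available for reanalysis. The article does not say whether the intent-to-treat or the per-protocol result takes precedence, but an article may leave that to the full protocol or analysis plan, so it is not part of this point.

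The study's exploratory label does not answer the concern. In this section it is the reason given for not correcting p-values, and it does not make an estimate unbiased.

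**Conclusion.** The point holds in a limited form. The plan commits to LOCF, gives no justification or alternative in the article, and expects drop-outs. Bias is absent only in special cases, such as no true difference with equal drop-out unrelated to outcome, or no change over time in the arm that loses patients. It does not depend on deterioration: improvement under exercise with a stable control is attenuated in the same way (0.50 to 0.425).

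Under the assumptions shown (linear change, ρ = 0.5), the false benefit runs from about 0 to 0.2 SD with 30%/30%/10% drop-out and a 0.5 to 1 SD common decline. Attenuation of a true effect is about 20% with 20% drop-out before week 3 in each arm. Direction and size cannot be fixed from the document.

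A reader might conclude that a mixed model does away with the problem. It does so only if data are missing at random; with early drop-out driven by unobserved worsening, about 0.08 SD remained. Severity: should-fix. The stated sample size is not affected.

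**What to change.** Replace the LOCF clause. Analyse all randomised patients as allocated with a likelihood-based mixed model for repeated measures (time, group, time-by-group, unstructured covariance), using every observed value and no single imputation. Keep LOCF at most as a sensitivity analysis. Add a short sensitivity analysis for drop-out that is missing not at random, for example assigning drop-outs progressively worse later values by arm and reporting how far the contrast moves.

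The cost is analysis wording only: no change to sample size, visits or patient burden. The article names SPSS; that it can fit such a model is general software knowledge, not something the article states. The downside is reliance on missing at random, which the added sensitivity analysis is there to test.

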### Ethical aspects

The study has been approved by the Ethikkommission Nordwest- und Zentralschweiz (EKNZ) (Switzerland; ProjectID 2018-01314), and the study is to be performed in accordance with the ethical principles laid down in the seventh and current edition (2013) of the Declaration of Helsinki. All eligible participants would be fully informed about the aims of the study and the confidential data handling. Although the interventions are not potentially risky, an insurance would be provided upon eligibility for participation. The insurance covers all damages and injuries occurring during the time a person is at the hospital to participate in the study.

### Protocol amendments

Important protocol modifications (i.e., change of assessment tools, inclusion, and exclusion criteria; change of interventions) would be communicated to the ethical committee (Ethikkommission Nordwest- und Zentralschweiz (EKNZ).

### Confidentiality and data protection

Participants would be fully informed and assured that their data are to be handled with highest confidentiality from the very beginning of the study, throughout the study and also afterward, once the study has been completed. Accordingly, no data and information would be shared with third parties. Staff members involved in the study would strictly comply with professional confidentiality. In this line, also members of the EKNZ ethical committee would be strictly obliged to respect medical confidentiality, and to strictly avoid any kind of divulgation of participants’ participation and data.

Only staff members of the present study are allowed to have access to the data and information of the study and participants. However, by law, members of the local ethical committee and members of the Swiss ethics committees on research involving humans are allowed to organize inspections and to get access to the source data. However, again, members of both authorities would strictly comply with professional confidentiality.

Data would be kept in an electronic database. Once a patient is enrolled in the study, she/he receives a study number, and the study number would be only visible in the database, while the principal investigator (DC) not otherwise involved in patients’ assessments and randomization has the patient sheet (“key”) with both patient’s name and her/his study number. In all of the files (Case Report Forms, statistic files, etc.) only patient’s study number would be registered.

### Monitoring

The source data/documents are accessible to independent monitors, who are not part of the research group, and questions are answered during monitoring. Again, audits and inspections of the authorities mentioned above may be performed to ensure proper study conduct and data handling procedures, as thoroughly described in the International Council of Harmonisation-Good Clinical Practice (ICH-GCP) guidelines and regulatory requirements.

### Study harms

After every intervention/session, participants would be investigated for any pain felt or other/additional unpleasant and unexpected sensations, which can be plausibly associated with the study intervention. Adverse events would be listed and discussed if the participant is to be excluded from the study.

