### Randomization

The randomizations are to be performed using an online software from the website Randomization.com (http://www.randomization.com). The online generator randomizes each subject to a single treatment using a method of randomly permuted blocks, with random block sizes for sex. Based on the generated list, a psychologist, not involved in the study, prepares 45 sealed envelopes, with no further identification, to be kept in an opaque and closed ballot box which are to be stirred before picking. Next, the psychologist would draw an envelope from the ballot and assign the study participants to one of the three study conditions picked. Once an envelope is drawn, it would be put aside. Experts rating the participants’ depression severity would be blinded to the participants’ study condition assigned.

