### Interventions

#### Endurance training

The endurance training will last for 6 consecutive weeks and consists of 2 weekly sessions (30–45 min each). Sessions would take place in small groups of 2 to 4 participants. After 5 min of warming-up and stretching, participants will exercise for 25–35 min on the treadmill at a pace of 11 to 14 points on the Borg Scale of ranging from 0 (complete rest or resting pace) to 20 (maximum pace), followed by 5 min of cooling down. In this study, cooling down represents light exercise to allow the body to gradually transition to a resting or near-resting state. Participants are allowed to adapt to their pace and to take breaks throughout the session, though they are also encouraged to keep both their speed and pace as long as possible.

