#### Active control condition

For 6 consecutive weeks, participants of the control condition will meet twice per week for 30–45 min but by contrast to the endurance and resistance training condition, the participants would not perform any planned physical exercise. Each session would take place in small groups of 2 to 4 participants. The control condition is not a ‘bona fide’ condition, which would be actually intended to elicit change [26, 27], that is to say, by default, group sessions in psychotherapy follow the aim to change participants’ dysfunctional cognitive-emotional concepts and information processing; By contrast, in the present control condition, topics such as successful coping strategies are not treated and not proactively proposed by the clinical psychologist responsible to monitor the content of the control conditions. Rather, the participants would be encouraged to proposing and exchanging daily life experiences.

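### The stated harms rule asks about post-session sensations plausibly linked to the intervention and may tie listing to exclusion, so harms would be incompletely recorded and open to attribution bias by arm

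*Protocol article*

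**What the plan says.** The Study harms section of the protocol article is the only text on how harms are collected. It makes two statements.

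- On inquiry: "After every intervention/session, participants would be investigated for any pain felt or other/additional unpleasant and unexpected sensations", followed directly by the qualifying clause "which can be plausibly associated with the study intervention".
- On listing: "Adverse events would be listed and discussed if the participant is to be excluded from the study".

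Other sections bear on how this rule would work:

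- All three arms have two sessions a week for 6 weeks. For the control arm, "participants of the control condition will meet twice per week for 30–45 min", but "the participants would not perform any planned physical exercise" (Active control condition).
- The only blinding stated concerns the depression ratings: "Experts rating the participants’ depression severity would be blinded to the participants’ study condition assigned" (Randomization).
- The dependent variables in Statistical analyses are psychological, sleep, quality-of-life and fitness measures. Adverse events are not among them.
- Table 1 schedules fitness and psychological assessments at weeks 0, 3 and 6.

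**The concern.** A harms procedure should first record what happened and then judge why. This text puts plausible causation into the description of what is looked for. An event thought to come from the tumour, chemotherapy or radiotherapy falls outside the stated inquiry, although it could be an exercise harm that was misjudged.

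This matters here because the Background places the training in the phase of adjuvant treatment after surgery, when events from disease and therapy are to be expected. A concurrent control arm with the same contact schedule is the natural means of separating those background events from harm due to exercise, but only if events are counted in the same way in each arm. A filter on plausible causation does not act equally on a treadmill session and a conversation.

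The last sentence adds a second difficulty. If listing depends on a possible exclusion, an event that is unpleasant but does not threaten participation may never be listed. The section Anticipated outcome and significance hopes that the results will support bringing regular exercise into the care of these patients. A reader weighing that step would want a harms record that does not depend on prior opinion about cause.

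**Working it through.** The plan gives no figure for harms, so there is none to reproduce. The check sets the texts side by side and then shows, on assumed values, how the filter acts.

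**Step 1: opportunity to report.** Each arm has 6 weeks × 2 sessions = 12 sessions (Endurance training, Resistance training, Active control condition). Inquiry after each session therefore gives every arm the same number of scheduled questions. The schedule itself introduces no difference between arms.

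**Step 2: what passes the filter.** The qualifying clause refers to the study intervention. In the exercise arms that is treadmill or resistance work, to which pain, dizziness or fatigue can readily be attributed. In the control arm it is conversation without planned exercise, to which few physical symptoms can be attributed. Equal asking need not give equal recording.

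**Step 3: what is listed.** The last sentence has two readings. Either events are listed and discussed when exclusion is in question, or events are listed and it is then discussed whether the participant must be excluded. On the first reading, listing is conditional on the exclusion decision. The text does not settle which is meant.

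**Step 4: form of the distortion.** Let n be the patients per arm, p the true risk of an event, a the probability that the event reaches an attended session, and q the probability that it is judged plausibly related. Then

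expected recorded events = n × p × a × q.

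With n, p and a equal across arms, the ratio of recorded events (exercise to control) is q_E / q_C, whatever the values of p and a.

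Only n = 15 comes from the document (Sample size calculation). The values of p, a and q below are **assumptions**, with the same true risk in each arm, so the true ratio is 1. With p = 0.20 there are 15 × 0.20 = 3 true events per arm.

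| a | q_E | q_C | Recorded, exercise arm | Recorded, control arm | Ratio |
|---|---|---|---|---|---|
| 1.0 | 0.8 | 0.2 | 3 × 0.8 = 2.4 | 3 × 0.2 = 0.6 | 4.0 |
| 1.0 | 0.9 | 0.5 | 3 × 0.9 = 2.7 | 3 × 0.5 = 1.5 | 1.8 |
| 1.0 | 0.5 | 0.5 | 3 × 0.5 = 1.5 | 3 × 0.5 = 1.5 | 1.0 |
| 0.7 | 0.8 | 0.2 | 3 × 0.7 × 0.8 = 1.68 | 3 × 0.7 × 0.2 = 0.42 | 4.0 |

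Two things follow. Counts fall whenever q is below 1, in every arm, so incomplete recording does not need any difference between arms. The ratio is distorted only when q differs by arm (or when a does). Non-attendance that is equal across arms lowers the counts but leaves the ratio unchanged.

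**The case against.** The strongest reply is that the text is short and loosely worded, and that this is a condensed article. Fuller adverse-event procedures may stand in the full protocol, and the article itself mentions case report forms, source documents, independent monitors and ICH-GCP. The inquiry covers any pain, the qualifying clause follows a comma and may merely describe the sensations sought, and the last sentence has a benign reading. This stands in part. That no inquiry is mentioned between sessions, at weeks 3 and 6, or after withdrawal is silence, and cannot be charged as a fault. The causality clause is different: it is a published condition, and additional detail elsewhere would have to override it.

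A reader might infer several stronger things that the document does not support.

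- *That a planned safety comparison is biased.* None is planned; adverse events are not among the variables in Statistical analyses.
- *That the control arm would record almost nothing by construction.* Session schedules are equal, and unpleasant sensations need not be physical: distress from talking about one's illness could qualify.
- *That causality is judged by staff who know the arm.* The section names neither the assessor nor the order of steps. That only the depression raters are said to be blinded makes it likely, but it remains an inference.
- *That events leading to drop-out are the most likely to be lost.* On the restrictive reading of the last sentence, events behind an investigator's decision to exclude are the ones that are listed. The worry could apply at most to patients who withdraw themselves.
- *That the small sample measures the fault.* With no events among 15 patients the one-sided 95% upper limit is 1 − 0.05^(1/15) = 18.1%, but this reflects sample size alone and would be the same under a better recording rule.
- *That the remark "Although the interventions are not potentially risky" in Ethical aspects supports the point.* It introduces a sentence on insurance and says nothing about recording.

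**Conclusion.** The point holds in a limited form. As written, the Study harms section confines its stated inquiry to sensations after sessions that are plausibly linked to the intervention, and leaves open whether listing depends on exclusion. Applied literally, it gives incomplete ascertainment in all arms, and any later account of harms by arm would be open to attribution bias.

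The size of the bias cannot be derived from the document. Its probable direction, towards relatively fewer recorded events in the control arm, rests on the assumption that physical symptoms are less readily attributed to talking sessions than to exercise. The ratios from 1.0 to 4.0 above are illustrations on assumed values, not estimates for this trial. The planned efficacy analyses are not affected. The change is worth making because it is cheap and because events not recorded at the time cannot be reliably recovered afterwards.

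**What to change.** Amend the Study harms section as follows.

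1. Delete the causality condition from the recording rule. Record every adverse event in all three arms regardless of presumed cause.
2. Ask after sessions and also at the existing week-3 and week-6 assessments, including patients who have stopped attending, where they can be reached.
3. Judge relatedness as a separate step, only after the event has been recorded.
4. Report counts by randomised arm.
5. Reword the last sentence so that listing does not depend on the exclusion decision, and keep the two matters in separate sentences.

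The contacts already exist, apart from reaching patients who no longer attend, so the cost is a few added questions and space on the case report form. The downside is a longer list, much of it probably due to the disease or its treatment. If the full protocol already records events in this way, only the published wording needs correcting.
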